Potential benefits for this approach includes (i) higher adherence to ART and retention in care, (ii) reduced per-patient cost of providing ART, by reducing the number of clinic visits required, (iii) decongestion of clinics to allow for increased capacity to manage patients newly diagnosed with HIV, those with infectious complications, treatment failure, and other co-morbidities and (iv) decreased waiting time and improved efficiency at clinics allowing for improved quality of care and patient satisfaction [7, 8].

Limited data are available from LMICs on multi-month scripting and dispensing and on studies using community-based models of care. A review of the literature reveals a lack of randomized studies of different ART dispensing intervals. An abstract presented at the Conference on Retroviruses and Opportunistic Infections, 2016 using Zambian data, suggested that requirements for monthly dispensing and/or systems that require multiple separate visits for refills and clinician evaluation can raise significant challenges for people living with HIV and result in treatment interruptions or complete disengagement from care [6].

This study’s primary objectives are (i) to determine if stable patients receiving 3 monthly dispensing of ART within CAGs have non-inferior retention in care and viral load suppression than stable ART patients receiving 3 monthly dispensing at health facilities after 12 and 24 months, (ii) 6 monthly dispensing of ART within the community from a health care worker have non-inferior retention in care than stable ART patients receiving 3 monthly dispensing at health facilities after 12 and 24 months and (iii) 6 monthly dispensing of ART within the community from a healthcare worker have non-inferior retention in care than stable ART patients receiving 3 monthly dispensing within CAGs after 12 and 24 months. The secondary objectives are to compare cost outcomes (cost per patient retained and cost per patient retained with viral suppression) between the three models, investigate the acceptability of 3 and 6 monthly community-based ART distribution among patients and service providers and to assess if there are measurable gains in clinic productivity realized following the introduction of community based MMD of ART.

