#### Costing and cost-effectiveness

A micro-costing approach, also known as the bottom-up method will be used. This will allow the tracking of every input in carrying out the study interventions. However, this approach will be supplemented by a macro-costing approach of fixed costs such as infrastructure, building, equipment, utilities etc. To ascertain the cost to provider, we will estimate the fixed and variable costs to care. Fixed cost to patients will include (i) equipment and vehicles (ii) building and Infrastructure and (iii) administration costs and other above point-of-care costs. As for variable costs, these will include but not limited (i) outpatient care (type and number of visits) (ii) Inpatient care (number of bed days in care) (iii) other services (ARTs, laboratory tests, non-ART drugs, consumables etc.).

Patient level costing, also known as direct non-medical costs will also be collected. These costs are borne by either the patient or relatives of the patient to improve the care towards the patient. This study intervention is expected to result in patient level benefits such as reduced cost for care seeking, productivity benefits due to reduced time spent seeking care and informal care effects. Data to assess patient level costs will be collected from a randomly selected sub-sample of patients from each arm. Costing outcomes will include:(i)average cost per patient retained in care and virally suppressed at 12 and 24 months (cost per patient retained)(ii)annual cost per patient in each cohort/arm (per patient year cost)(iii)cost-effectiveness of the intervention arms will be compared with respect to retention in care and viral suppression.

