#### Statistical analysis, power and sample size considerations

Descriptive data of the study population stratified by treatment arm will presented as medians and interquartile ranges for continuous variables and proportions for categorical variables.

Our analysis will use an intention-to-treat approach in which generalized estimating equations (GEE) will be computed to estimate risk differences and risk ratios and associated 95% confidence interval for the effect of each intervention arm compared to the control (Patients receiving 3 monthly ART supply at facilities), specifying for clustering by facility. A small cluster size variance correction will be used. Should we identify any baseline imbalances between study arms, we will adjust for these through multivariable regression models and report adjusted effect measures and corresponding 95% confidence intervals.

Qualitative analysis will be employed in this study to ascertain feasibility, acceptability of CAGs and community ART distributions by patients and service providers. Summative content analysis which involves counting and comparisons of keywords or content, followed by the interpretation of the underlying context will be conducted. The data will be further analysed for emerging key themes and the findings will be interpreted based on each research question. Quotes will also be extracted for each of the themes that emerge from the data. It is anticipated that MMD will reduce both facility and patient costs of treatment and that it will be cost-saving compared to standard of care. For facilities, fewer clinic visits by patients should save the time of providers and support staff. For patients, fewer clinic visits are expected to reduce the costs of travel and to save time. The study will estimate differences in both provider and patient costs. Cost-effectiveness will be estimated as the average cost per successful outcome (patient retained at 12 and 24 months).

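### The stated cost-effectiveness measure is an average cost per retained patient by arm; the planned cost and retention differences are never combined, so the trade-off between them is not estimated

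*Protocol article*

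**What the plan says.** The section on statistical analysis, power and sample size names the measure: "Cost-effectiveness will be estimated as the average cost per successful outcome (patient retained at 12 and 24 months". The secondary objective in the Background is to "compare cost outcomes (cost per patient retained and cost per patient retained with viral suppression) between the three models". The costing section lists three outcomes: "average cost per patient retained in care and virally suppressed at 12 and 24 months (cost per patient retained"), then "annual cost per patient in each cohort/arm (per patient year cost"), and third that "cost-effectiveness of the intervention arms will be compared with respect to retention in care and viral suppression". The third names no measure of its own.

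The analysis section also plans the two ingredients of an incremental comparison, separately. For cost: "The study will estimate differences in both provider and patient costs". For effect, estimating equations will "estimate risk differences and risk ratios and associated 95% confidence interval for the effect of each intervention arm compared to the control". Nowhere does the article name an incremental ratio, a net benefit or any other joint analysis of the two differences.

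**The concern.** An average ratio divides an arm's cost by its own successes. Comparing two such ratios does not say what is gained or given up in moving from one arm to the other; that needs the difference in cost set against the difference in effect. A cheaper arm that retains fewer patients has the lower ratio whenever its cost relative to control is below its retention relative to control, however the lost patients are valued.

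This design makes that pattern plausible. The trial tolerates some loss of retention by construction, and multi-month dispensing is expected to reduce costs. If a community arm ends up cheaper and slightly worse, a policy reader needs to know how much is saved for each additional patient not retained. The named measure does not answer this, and separate intervals for cost and retention do not give the joint uncertainty.

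A smaller matter sits beside it. The Background lists two cost outcomes, one for retention and one for retention with suppression. The first outcome in the costing section requires both retention and suppression but carries the label of the retention-only outcome, while the analysis section uses retention alone.

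**Working it through.** **Inputs from the article (Sample size estimate).** Attrition 5% at 12 months, so 95% retained; non-inferiority limit 3.25 points; one-sided α 0.05; power 85%; intra-cluster correlation 0.01; 192 per facility; 1,920 per arm.

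**The plan's own figure.** No cost figure is stated, so the only figure to reproduce is the sample size, which supplies the retention inputs.
- Before clustering: (1.645 + 1.036)² × (2 × 0.95 × 0.05) / 0.0325² ≈ 647 per arm.
- Design effect: 1 + 191 × 0.01 = 2.91.
- Product: 647 × 2.91 ≈ 1,883 per arm, against 1,920 stated. Power at 1,920 is 85.6%, against 85% stated. The inputs are read correctly.

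**Assumptions.** The control's annual cost per patient is set to 100. A non-retained patient accrues a fraction *f* of a year's cost, and *f* is varied.

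**Average ratio.** With annual cost *c* and attrition *a*, cost per retained patient = *c* × [(1 − *a*) + *a f*] / (1 − *a*). The table compares *a* = 0.05 (control) with *a* = 0.0825 (an arm at the limit), both at *c* = 100. The break-even saving is 1 minus the first ratio divided by the second.

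| *f* | Control | Arm at limit | Break-even saving |
|---|---|---|---|
| 0.25 | 101.3 | 102.2 | 0.9% |
| 0.50 | 102.6 | 104.5 | 1.8% |
| 0.75 | 103.9 | 106.7 | 2.6% |
| 1.00 | 105.3 | 109.0 | 3.4% |

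At *f* = 1 the result is simply 1 − 0.9175/0.95 = 3.4%, which is also the answer if cost per enrolled patient is held fixed.

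**What the ratio leaves out.** Give the arm at the limit a 5% lower annual cost (*c* = 95).
- *f* = 0.5: the ratio is 95 × 0.95875 / 0.9175 = 99.3, against 102.6 for control, so the arm ranks better. Cost per enrolled patient is 95 × 0.95875 = 91.08 against 100 × 0.975 = 97.50, a saving of 6.42. Divided by 0.0325, that is about 198 saved per additional patient not retained.
- *f* = 1: the ratio is 95 / 0.9175 = 103.5, against 105.3. The saving is 5 per enrolled patient, and 5 / 0.0325 ≈ 154 per additional patient not retained.

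In both cases the ratio says only that the community arm is lower. The quantity needed for a decision is the 154 or 198, which the plan does not name.

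**How far this can coexist with a non-inferiority claim.** An arm passes if its excess attrition *d* plus 1.645 standard errors is below 0.0325. With SE = √{[0.95 × 0.05 + (0.95 − *d*)(0.05 + *d*)] × 2.91 / 1920}, the solution is *d* ≈ 0.0117 (SE ≈ 0.0126; 0.0117 + 1.645 × 0.0126 ≈ 0.0325). So an arm passes only below about 1.2 points of excess attrition. At that point the break-even saving is about 0.6% for *f* = 0.5 and 1.2% for *f* = 1.

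**The case against.** **The plan already estimates both differences.** True. Cost differences and retention risk differences with confidence intervals are planned, and retention is a primary outcome. A reader might infer that the ratio will hide a loss of patients; the document does not support that for the report as a whole. What stands is narrower: the two differences are not joined, and the measure called cost-effectiveness is not built from them.

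**The ratio reacts more than partial accrual suggests.** Also fair. The sections on end points and on comorbidities and pregnancy count some patients as not retained although they stay in care under observation, some with more frequent visits. They go on accruing cost. In the 6-month arm half a year's drugs are issued at enrolment. Values of *f* near 1 are therefore realistic, and above 1 is possible (an assumed 1.25 gives a break-even of 4.2%). No single small threshold should be quoted; the range is the honest statement.

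**An arm observed at the limit would fail the primary comparison.** Correct, as the last step of the working shows. The trade-off still arises, on a smaller scale, for an arm that passes with up to about 1.2 points of excess attrition.

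**No wrong decision is demonstrated.** Correct. Whether 154 or 198 per additional patient not retained is acceptable depends on a valuation that the documents do not give.

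**Cost per patient retained is itself the stated objective, and detail may sit in a fuller plan.** The measure does answer that objective as worded. But the article also promises a cost-effectiveness comparison of arms and names its estimator, so this is a stated choice and not an omission.

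**The standard-of-care remark.** The article anticipates that "it will be cost-saving compared to standard of care". A reader might infer a wrong economic comparator. The remark is an expectation only; the effect analyses compare with 3MF.

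**Conclusion.** The point holds in a limited form. The named estimator is an average ratio by arm, and it cannot show the saving per additional patient not retained. The by-arm reading is an inference from the Background and the costing section, but a clear one. On the article's retention figures and assumed costs, an arm at 91.75% retained draws level with a control at 95% once its annual cost is about 0.9% to 3.4% lower, for accrual of 25% to 100% of a year's cost by non-retained patients.

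The weakness is in the ratio, not in the whole report. It concerns a secondary outcome and leaves the primary conclusion untouched. It does not show that patient losses would go unreported or that a wrong policy choice would follow. The mislabelled costing outcome is a minor inconsistency that stands on the text alone. The change is worth making because it reuses data already planned.

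**What to change.** Replace the estimator sentence with an incremental one. For each community arm against 3MF, and for 6MCD against 3MC, report the incremental cost per enrolled patient jointly with the incremental proportion retained, and separately with the incremental proportion retained and suppressed. Present the result as an incremental cost-effectiveness ratio or as net benefit, with joint uncertainty that respects clustering by facility, for example by resampling whole facilities. Keep average cost per success as a descriptive figure.

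Reconcile the first outcome in the costing section with the two outcomes in the Background: give cost per patient retained and cost per patient retained with suppression each its own label, and have the analysis section refer to both.

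Cost: changed wording and a little more analysis work, with no new data collection. The downside is that incremental ratios carry wider uncertainty than arm averages.

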### Sample size estimate

Sample sizes were determined for a cluster randomized non-inferiority trial with retention in care at 12 months as the primary outcome. A total of 30 study sites will be available for randomization, with three study arms, 10 clusters per arm, and participant enrolment numbers will be assumed to be equal at each site. The probability of patient attrition 12 months after study enrolment is assumed to be 5%. An intra-cluster correlation coefficient of 0.01 for patient retention/attrition amongst stable ART patients is assumed from a previous cluster randomized trial including stable ART patients [9]. The non-inferiority limit is specified as 3.25%. Assuming α = 0.05, power of 85%, and using a one-sided Z-test (un-pooled) statistic, approximately 192 enrolled participants per facility will be required with a total sample size of 5760 participants, representing 1920 participants per arm.

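### The 85% power belongs to a one-sided 0.05 z-test, but the only intervals planned are 95% CIs and no rule links the two; read from a two-sided 95% CI, power is about 73–77%

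*Protocol article*

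**What the plan says.** In the protocol article, the section Sample size estimate fixes the test used for sizing, with α set at 0.05: "power of 85%, and using a one-sided Z-test (un-pooled) statistic". The other inputs are in the same section:

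- Attrition: "The probability of patient attrition 12 months after study enrolment is assumed to be 5" per cent.
- Margin: "The non-inferiority limit is specified as 3.25" per cent.
- Correlation: "An intra-cluster correlation coefficient of 0.01 for patient retention/attrition amongst stable ART patients is assumed".
- Clusters: "A total of 30 study sites will be available for randomization, with three study arms, 10 clusters per arm".
- The resulting size is 192 participants per facility, 1920 per arm and 5760 in all.

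The section Statistical analysis, power and sample size considerations describes the inference. GEE models are to give "risk differences and risk ratios and associated 95% confidence interval for the effect of each intervention arm compared to the control". Adjusted estimates, if needed, also come with 95% intervals. On the standard error it says only: "A small cluster size variance correction will be used". It names neither the type of correction nor a reference distribution.

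The article mentions no 90% interval and no one-sided bound outside the sample size section. It does not say which limit is to be compared with the 3.25-point margin.

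**The concern.** A one-sided test at 0.05 corresponds to the limit of a two-sided 90% interval. The limit of a two-sided 95% interval is a one-sided test at 0.025. The article sizes the trial on the first and reports the second, so the printed power and the printed interval describe different procedures.

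Two consequences follow. If non-inferiority is judged from the 95% interval, the trial has clearly less power than stated. If it is judged at one-sided 0.05, the same report can claim non-inferiority and show a 95% interval that includes differences beyond the margin. With no rule linking the two, identical data can support either conclusion. The trial is meant to inform policy, so the choice should be fixed before results are seen. The article says enrolment was still under way, so it could be.

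**Working it through.** **Inputs from the article:** 10 facilities per arm, 192 participants each, equal enrolment, 12-month attrition 5%, ICC 0.01, margin 3.25 points, one-sided α 0.05, unpooled z-test.

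**Assumptions added here:** true difference zero (5% attrition in both arms); where a t value is used, 18 df (20 clusters compared, minus 2) or 27 df (30 clusters, minus 3).

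**Step 1. Standard error.**
- Design effect = 1 + (192 − 1) × 0.01 = 2.91.
- SE = √(2 × 0.05 × 0.95 × 2.91 / 1920) = 0.0120, or 1.20 percentage points.
- Margin / SE = 0.0325 / 0.0120 = 2.708 (unrounded SE).

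**Step 2. Reproduce the stated power.** One-sided 0.05 with z: Φ(2.708 − 1.645) = 85.6%, against 85% stated. The exact requirement is about 182 per facility, so 192 is slightly generous. Evaluating the test arm's variance at 8.25% attrition gives 76.8% instead, which does not reproduce the figure. The zero-difference reading is therefore the one that fits.

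**Step 3. The same design read from a two-sided 95% interval.** One-sided 0.025 with z: Φ(2.708 − 1.960) = 77.3%.

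**Step 4. t in place of z** (noncentral t, noncentrality 2.708):

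| Critical value | One-sided 0.05 | One-sided 0.025 |
|---|---|---|
| z | 85.6% | 77.3% |
| t, 27 df | 84.0% | 74.3% |
| t, 18 df | 83.1% | 72.6% |

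Most of the loss comes from the change of α. The t value takes a further 3 to 5 points at 0.025.

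**Step 5. Effect of the variance correction.** The article plans a variance correction, which is not the same thing as t degrees of freedom. A simulation checked the combinations: 200,000 trials, beta-binomial, 10 against 10 clusters of 192, same inputs.

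| Correction and critical value | One-sided 0.05 | One-sided 0.025 |
|---|---|---|
| Kauermann-Carroll type, z | 85.2% | 77.3% |
| Kauermann-Carroll type, t 18 df | 83.2% | 73.2% |
| Mancl-DeRouen type, z | 83.2% | 74.2% |
| Mancl-DeRouen type, t 18 df | 80.8% | 69.7% |

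The corrected analyses run from about 81% to 85% at one-sided 0.05 and from about 70% to 77% at one-sided 0.025. The uncorrected sandwich estimate with z gives 87.0% and 80.0%. Those figures are higher because that estimate is biased downward with so few clusters. It follows that 77% is compatible with a corrected variance.

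**Step 6. How often the two rules disagree.** With SE 1.20 points:
- One-sided 0.05 is passed if the observed attrition excess is below 3.25 − 1.645 × 1.20 = 1.28 points.
- The 95% interval stays below the margin only if the excess is below 3.25 − 1.960 × 1.20 = 0.90 points.
- With no true difference, the excess falls between 0.90 and 1.28 with probability 85.6% − 77.3% = 8.3% per comparison.

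**Step 7. Scale of the gap.** To have 85% power from a two-sided 95% interval with 10 clusters per arm and z, the effective size is 808 per arm, which needs about 416 per facility in place of 192.

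**The case against.** The strongest reply is that nothing in the sample size section is wrong. It names its test, and the power follows from it. One-sided 0.05 is a legitimate choice, and it is the only error rate the article gives for non-inferiority. The 95% intervals may be there for estimation and reporting only. On that reading, power under z, or under t with an unbiased variance, is about 83–85%, so the shortfall is 0 to 2 points, and about 4 points under the most conservative combination. The deciding interval is also something a condensed article may leave to the full protocol or SAP.

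Much of this stands. A reader might infer that the 85% is a calculation error, or that the trial's true power is 73%. The documents support neither. The calculation reproduces, the article never says the 95% interval decides, and the correction type and degrees of freedom behind any single lower figure are unstated.

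What the reply does not remove is the mismatch in the printed text. The point is not that a detail is absent. The article fixes a sizing test and, separately, fixes the interval to be reported, and the two do not correspond. A later document can choose between them, but it cannot make 85% the power of a two-sided 95% interval. If it chooses one-sided 0.05, the possible conflict between the claim and the reported interval remains.

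**Conclusion.** The concern holds as a mismatch between the stated power and the planned interval, at moderate severity. The 85% is correct for a one-sided 0.05 z-test. It does not describe a non-inferiority judgement made from a two-sided 95% interval, for which power is about 77% with z and 73–74% with t, within an overall range of about 70–77%. That is roughly 8 to 15 points below the stated figure. If one-sided 0.05 is the intended rule, power is about 81–85%, and the remaining problem is the roughly 8% chance per comparison, with no true difference, that the two rules disagree.

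These figures rest on the article's own attrition, ICC, margin and equal facility sizes, and on assumptions it does not state: a true difference of zero, 18 or 27 degrees of freedom, and the two common variance corrections tried here. Which figure applies cannot be settled until the decision rule is stated.

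**What to change.** State one decision rule and make the reported interval and the power agree with it. Either:

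- **(a)** non-inferiority is concluded if the upper limit of the two-sided 95% CI for the attrition risk difference lies below 3.25 points, with power restated as about 73–77%; or
- **(b)** one-sided 0.05 is kept, the 90% CI (one-sided 95% bound) is named as the deciding interval and reported, and power is restated as about 83–85%.

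In both cases, name the variance correction, the reference distribution and any degrees of freedom behind the restated figure. A Mancl-DeRouen-type correction with t on 18 df would put it nearer 70% under (a) and 81% under (b).

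The cost is a few sentences and, in most cases, a less favourable stated power. Neither option needs more patients or a change in trial conduct.
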